#### Principle of analysis

All analyses will be by the intention-to-treat (ITT) principle which included all randomized patients who received the TXYF or its placebo and returned for at least one follow-up appointment. The per-protocol set (PPS) analysis for the primary outcomes is being conducted in conjunction with the ITT analysis. When the results of ITT and PPS analysis are conflict, the results of ITT analysis will be given preference. When the results of ITT and PPS analysis are consistent, the reliability of the results can be increased. ITT will be used for the analysis of baseline characteristics, and safety set (SS) will be used for the safety evaluation.

#### Statistical description and statistical analysis methods

With regard to continuous outcomes, Q-Q plots will be used to evaluate normality assumptions. Continuous outcomes conforming to the normal distribution will be presented as mean ± standard deviation (SD) and non-conforming to the normal distribution will be presented as median and interquartile range (IQR) [41]. For both primary continuous outcomes and secondary continuous outcomes, simple or multiple linear regression will be applied to estimate the difference between TXYF group and placebo group. Two preadjusted analyses will be conducted, if appropriate. The first preadjusted regression analysis included only baseline variables (e.g., age, gender, smoking and drinking). The second preadjusted analysis will also adjust for concomitant treatment, a variable thought to be associated with outcome but not affected by treatment allocation.

Categorical data will be expressed by the number and percentage of occurrences. For primary and secondary categorical outcomes, differences will be compared using chi-squared tests and, if appropriate and necessary, logistic regression. The preadjusted analyses will be conducted that adjust for the same covariates as those described for the continuous outcomes.

Estimates of treatment effect will be reported with 95% confidence intervals. Two-tailed *P*-values ≤ 0.05 will be considered statistically significant.

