#### Secondary outcomes

(a) Stool frequency: the average daily number of spontaneous defecation recorded in the week before each time-point; (b) stool consistency measured using the Bristol stool scale [33]; (c) quality of life measured using the scale of IBS-quality of life (IBS-QOL) [34]; (d) anxiety measured using the self-rating anxiety scale (SAS) [35]; (e) depression measured using the self-rating depression scale (SDS) [36]; (f) the safety using TXYF and placebo, which will be evaluated in the following aspects: (1) routine examination (blood routine, urine routine, stool routine + occult blood (OB)); (2) biochemical indexes including liver function (aspartate aminotransferase (AST) and alanine aminotransferase (ALT)), kidney function (blood urea nitrogen (BUN), creatinine); (3) heart electrical activity measured using electrocardiogram; (4) adverse events, such as rash, constipation, or other special symptoms, recorded at any time during the treatment by the patient: incidence of adverse events = (number of adverse events/total cases) × 100%; (5) severe adverse events, such as loss of function or disability, life-threatening or even death, recorded at any time during the treatment by the researchers: incidence of severe adverse events = (number of severe adverse events/total cases) × 100%.

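### A few symptomless rises in liver, kidney or blood-count values would be largely hidden by the stated regression rule and left out of the adverse-event incidence

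*Protocol article*

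**What the plan says.** In the protocol article, Secondary outcomes, item (f) is "the safety using TXYF and placebo, which will be evaluated in the following aspects". The aspects include "routine examination (blood routine, urine routine, stool routine + occult blood (OB") and "biochemical indexes including liver function (aspartate aminotransferase (AST) and alanine aminotransferase (ALT)), kidney function (blood urea nitrogen (BUN), creatinine"), followed by the electrocardiogram, adverse events and severe adverse events. Non-severe events are worded as "adverse events, such as rash, constipation, or other special symptoms, recorded at any time during the treatment by the patient". Severe events are recorded by the researchers and are illustrated by disability, threat to life and death.

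Under Statistical description and statistical analysis methods there is one rule for continuous data: "For both primary continuous outcomes and secondary continuous outcomes, simple or multiple linear regression will be applied to estimate the difference". Variables "non-conforming to the normal distribution will be presented as median and interquartile range (IQR"). For the rest, "Categorical data will be expressed by the number and percentage of occurrences", with chi-squared tests or logistic regression.

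Principle of analysis gives the safety evaluation its own population, the safety set. No section gives it its own method. The Statistical analysis section refers to a separate statistical analysis plan, which is not shown.

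**The concern.** Drug-related organ injury usually appears as a large change in a few individuals, not as a shift of the whole arm. A median with an interquartile range hardly responds to a few extreme values. A mean difference does respond, but the same values inflate its standard error. The stated method therefore suits efficacy scores and not numeric safety tests.

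The adverse-event rule does not close the gap. A raised ALT or creatinine without symptoms is not something a patient notices or records, and unless it is severe it is not in the researchers' category either. It would then be missing from the incidence that the protocol defines.

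Safety is one of the trial's two stated aims, and the Discussion looks ahead to use in routine care. A non-significant difference in mean ALT, together with a symptom-based event count, could reassure readers when individual signals are present.

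**Working it through.** **Which rule applies to which result**

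| Safety item | Nature of the result | Rule as worded |
|---|---|---|
| AST, ALT, BUN, creatinine, blood counts | numeric | mean/SD or median/IQR, then linear regression |
| Urine, stool, occult blood, ECG findings | largely categorical | number and percentage |
| Non-severe adverse events | symptoms recorded by the patient | incidence of adverse events |
| Severe adverse events | recorded by researchers | incidence of severe adverse events |

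A symptomless, non-severe abnormality in the first row appears in that row only.

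**How well the numeric rule shows a few cases**

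The protocol states no figure on this point, so there is none to reproduce. The input from the document is 48 patients per arm (Sample size). The assumptions are ALT lognormal with median 20 U/L and log-SD 0.4, an upper limit of normal of 40 U/L, and k TXYF patients set to 3 times (120 U/L) or 5 times (200 U/L) that limit, with none on placebo. Simple linear regression on treatment group is the two-sample t-test. Each row below rests on 20,000 simulated trials.

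The expected mean difference can be checked by hand. The lognormal mean is 20 × exp(0.4²/2) = 21.7 U/L, and the difference is k × (x − 21.7)/48. For k = 2 and x = 200 this is 2 × 178.3/48 = 7.4 U/L.

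| k of 48 | Value, U/L | Mean difference | Median difference | P ≤ 0.05 |
|---|---|---|---|---|
| 2 | 120 | 4.1 | 0.4 | 8% |
| 2 | 200 | 7.4 | 0.4 | 3% |
| 3 | 120 | 6.1 | 0.7 | 19% |
| 3 | 200 | 11.2 | 0.7 | 16% |
| 4 | 120 | 8.2 | 0.9 | 41% |
| 4 | 200 | 14.9 | 0.9 | 53% |

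A second set of assumptions (median 22 U/L, log-SD 0.38, cases at 200 U/L) gives about 4% for k = 2 and 17% for k = 3.

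**Why a larger elevation does not help**

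Let k of n patients in one arm have a value so large that all other variation is negligible. The mean difference is then kx/n and its squared standard error is k(n − k)x²/[n²(n − 1)]. The x cancels, which leaves t = √[k(n − 1)/(n − k)]. With n = 48:

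- k = 2: √(2 × 47/46) = 1.43
- k = 3: √(3 × 47/45) = 1.77
- k = 4: √(4 × 47/44) = 2.07

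The two-sided 5% critical value on 94 degrees of freedom is 1.99. With 2 or 3 cases the statistic therefore settles below it, however extreme the elevations are. This limit does not depend on the assumed ALT distribution.

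**What a count would show**

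Fisher's two-sided P for k v 0 of 48 is 2 × C(48,k)/C(96,k):

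- 2 v 0: 2 × 1128/4560 = 0.49
- 3 v 0: 2 × 17,296/142,880 = 0.24
- 4 v 0: 2 × 194,580/3,321,960 = 0.12

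Exact (Clopper-Pearson) 95% intervals are 0.5% to 14.3% for 2/48 and 1.3% to 17.2% for 3/48. The count is no more significant than the regression, but it puts the cases and their uncertainty on the page.

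**The case against.** The strongest reply is that abnormality thresholds, shift tables and patient listings belong in the statistical analysis plan, which the article cites and which is not shown. That stands: their absence is not the point made here. The point is that the article does state a method for continuous secondary outcomes and a source for non-severe adverse events, and both suit numeric safety tests badly. An analysis plan that followed them would inherit both.

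It can also be said that the regression sentence names no laboratory test, and that results classed as normal or abnormal would fall under the categorical rule. That reading is possible. But the tests are listed within a secondary outcome, numeric values are continuous as collected, and neither classification nor exemption is stated.

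Three stronger readings are tempting and are not supported:

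- A reader might infer that adverse events are only those a patient records. Researchers record the severe ones, and the trial quality control section makes monitors responsible for timely recording and reporting.
- A reader might infer that organ toxicity would be invisible. The tests are still done and form safety aspects of their own, the Q-Q plots would show extreme values, and nothing forbids listing individual results.
- A reader might extend the regression criticism to every safety test. ECG, urine, stool and occult-blood findings are largely categorical and already come as number and percentage.

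Nor does the document say that a non-significant laboratory difference will be taken as proof of safety. That is a risk of interpretation, not a stated plan.

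**Conclusion.** The concern holds for numeric liver, kidney and blood-count values and for symptomless, non-severe laboratory abnormalities. For these the stated summaries would largely hide a few affected patients, and the stated adverse-event rule would not count them. Under the assumed ALT values, regression flags 2 or 3 cases among 48 in about 3% to 19% of trials. At 4 cases it flags them in roughly half (41% to 53%), so the weakness is specific to small numbers of cases. The ALT median, spread, upper limit and size of elevation are illustrative assumptions; only the 48 per arm is from the protocol.

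Counting patients does not cure the low power of a trial this size. What it adds is visibility. Confidence is moderate, because the unseen analysis plan may already report abnormal values by patient. The change should be made, but the point does not threaten the trial's primary result.

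**What to change.** Under Statistical description and statistical analysis methods, add that numeric safety laboratory values will be reported per arm, in the safety set, as the number and percentage of patients who go from normal at baseline to abnormal, with exact 95% confidence intervals, instead of relying on a regression difference. The definition of abnormal can be left to the statistical analysis plan.

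Under Secondary outcomes, item (f), state that clinically significant laboratory or ECG abnormalities identified by the researchers count as adverse events, alongside the symptoms that patients record.

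Both changes are wording and tables from data already being collected, and no new tests are needed. The downside is a slightly higher reported adverse-event percentage.

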#### Participant inclusion criteria

The included participants must meet all the following criteria: (a) patients aged between 18 and 65 years, male or female; (b) patients who meet IBS-D Rome IV diagnostic criteria [9]; (c) patients who meet Liver Depression and Spleen Deficiency Syndrome (Ganyu Pixu Zheng) from the diagnostic criteria for TCM syndromes (2017) [26]; (d) irritable bowel syndromes symptom severity score (IBS-SSS) ≥ 75 points; (e) patients who have not taken any medications related to the treatment of IBS-D at least 1 week before enrolling the trial and have not participated in other ongoing trials; (f) patients who have had a colonoscopy within 1 year and had an examination report; (g) patients who have accepted to participate in the trial voluntarily and have signed the informed consent form. The informed consent process complies with Good Clinical Practice (GCP); (h) long-term (at least 6 months) residence in the place where the treatment is given.

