#### Primary outcomes

The degree of IBS symptom severity, measured using the scale of irritable bowel syndromes symptom severity score (IBS-SSS) [32]. The disease severity will be divided into four levels base on IBS-SSS: normal (the score < 75), mild (75 ≤ the score < 175), moderate (175 ≤ the score < 300), and severe (the score ≥ 300). If the disease severity remains at the original (baseline) level or changes to higher level (e.g., from mild to moderate) after treatment, it will be judged as no response; otherwise, it will be considered response. The response rate = (total number of participants − number of no response participants)/total number of participants × 100%. Finally, we will not only compare the scores after treatment between groups, but also compare the response rate.

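### The main IBS-SSS score comparison does not name baseline IBS-SSS as a covariate, so a precision gain from data already held is left unsecured

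*Protocol article*

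**What the plan says.** Under Primary outcomes, the protocol article states that "we will not only compare the scores after treatment between groups, but also compare the response rate". The score comparison is therefore on values after treatment.

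Under Statistical description and statistical analysis methods, for continuous outcomes, "simple or multiple linear regression will be applied to estimate the difference between TXYF group and placebo group". The adjusted versions are conditional: "Two preadjusted analyses will be conducted, if appropriate". The first of them "included only baseline variables (e.g., age, gender, smoking and drinking", and "The second preadjusted analysis will also adjust for concomitant treatment". The categorical outcomes are to use the same covariates.

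Baseline IBS-SSS is not mentioned in the analysis text, but it is available. Participant inclusion criteria require "irritable bowel syndromes symptom severity score (IBS-SSS) ≥ 75 points", and the response definition compares each participant's severity level after treatment with the level at baseline.

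**The concern.** When an outcome is a repeated measurement of the entry score, the entry score usually carries more information about the final value than age, gender or lifestyle variables do. Including it removes the part of the outcome variance that baseline severity explains. Three features of the text mean that this is not secured:

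- Simple regression is allowed as the analysis, which means no adjustment at all.
- All four example covariates are demographic or lifestyle variables.
- One covariate set serves every outcome, continuous and categorical. An outcome's own baseline differs from outcome to outcome, so a shared list does not naturally contain it.

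The population also leaves room for baseline severity to vary. Eligibility sets a lower IBS-SSS limit of 75 and no upper limit, so mild, moderate and severe patients can all enter, and the randomisation section mentions no stratification by severity. What is at stake is the width of the confidence interval and the power of the score comparison, not its validity.

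**Working it through.** **The plan's own figure.** The only sample-size figure is for response: 73% against 43%, margin 10%, giving 48 per group. Its inputs include no IBS-SSS standard deviation, mean difference or baseline-to-final correlation, so the plan has no figure for score precision to reproduce. Put into the printed formula, those inputs give (1.96 + 0.842)² × (0.73 × 0.27 + 0.43 × 0.57) / 0.20² = 86.8 per group before dropout, which does not match 48. That is a separate matter and does not affect the calculation below.

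**Inputs.**
- Evaluable per arm: 48 × 0.9 = 43.2, taken as 43 (Sample size section, 10% loss).
- Test: two-sided at 0.05 (statistical methods section).
- r, the within-arm correlation of baseline with post-treatment IBS-SSS: not in the document. Assumed 0.2 to 0.6.
- Effects are in units of the post-treatment standard deviation (SD), because no SD is given.

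**Formulas** (normal approximation).
- Unadjusted: standard error (SE) = √(2/n) SD = √(2/43) = 0.216 SD.
- Adjusted for baseline: SE ≈ √(2/n) × √(1 − r²) SD, so the variance is multiplied by 1 − r².
- Difference detectable with 80% power, unadjusted: 0.216 × (1.96 + 0.842) = 0.604 SD.
- Power at that same difference after adjustment: Φ(2.802/√(1 − r²) − 1.96). For r = 0.5 this is Φ(2.802/0.866 − 1.96) = Φ(1.275) = 89.9%.

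| Assumed r | Variance factor 1 − r² | Variance reduction | SE factor | Power at 0.604 SD | Detectable difference (SD) |
|---|---|---|---|---|---|
| none (unadjusted) | 1.00 | 0% | 1.00 | 80.0% | 0.60 |
| 0.2 | 0.96 | 4% | 0.98 | 81.6% | 0.59 |
| 0.3 | 0.91 | 9% | 0.95 | 83.6% | 0.58 |
| 0.4 | 0.84 | 16% | 0.92 | 86.4% | 0.55 |
| 0.5 | 0.75 | 25% | 0.87 | 89.9% | 0.52 |
| 0.6 | 0.64 | 36% | 0.80 | 93.8% | 0.48 |

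**Chance imbalance.** The baseline means of the two arms differ by chance with SE 0.216 baseline SD. An imbalance at the 95% limit is 1.96 × 0.216 = 0.42 SD. It moves the unadjusted post-treatment difference by r × 0.42: 0.08 SD at r = 0.2, 0.17 at 0.4 and 0.25 at 0.6. The unadjusted interval already allows for this on average over randomisations. Adjustment removes it in the trial actually run.

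**Response endpoint.** The factor 1 − r² belongs to the linear model and says nothing about the logistic one. What can be read from the cut-points is that response depends on where in a band a patient starts. From 80, a fall of just over 5 points is enough to get below 75; from 174, a fall of more than 99 is needed; from 180, in the next band, just over 5 again takes the patient below 175. The dependence restarts at each cut-point, so a single straight-line term in the baseline score would fit it poorly.

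**The case against.** The strongest case against is that this is detail left open, not an error. The covariates are introduced as examples, the only limit is that they be baseline variables, and baseline IBS-SSS is one. Comparing scores after treatment names the outcome and is compatible with ANCOVA, which models the same outcome. The article also refers to a statistical analysis plan that is not shown and may name the covariate. All of this stands, and it rules out one tempting inference: that the plan excludes baseline IBS-SSS and will throw the precision away. The text does not show that.

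What the objection does not remove is that the article is not silent on adjustment. It sets out a strategy, makes it conditional and gives four examples, none of them the baseline of the outcome. A fully compliant analysis could omit it.

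Four further readings are not supported:

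- That the unadjusted comparison is biased. It is not, after randomisation.
- That the omission costs the equivalent of raising 96 patients to 96/0.84 = 114 or 96/0.64 = 150. Those figures follow from r = 0.4 and 0.6, but r is assumed, and 96 was set on the response rate, not the score.
- That adding baseline severity to the logistic model would narrow the odds-ratio interval. Odds ratios are non-collapsible: a prognostic covariate changes the quantity being estimated and generally increases the standard error of the log odds ratio, even where power improves.
- That every secondary outcome has the same gain ready to use. The schedule in Table 1 is not shown, so baseline collection of IBS-QOL, SAS, SDS and the stool measures cannot be confirmed.

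**Conclusion.** The point holds as an improvement available at almost no cost, not as a flaw in validity. The score analysis as written may be run without baseline IBS-SSS, which the trial must hold for each participant. Naming it would cut the variance of the treatment difference by 4 to 9% if r is 0.2 to 0.3, which is small, and by 16 to 36% if r is 0.4 to 0.6, which is material. At a difference for which the unadjusted test has 80% power with 43 per arm, power would become about 82 to 84% in the lower range and 86 to 94% in the upper.

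These sizes rest on an assumed r, a roughly linear relation between baseline and final score, and 10% loss. They apply to the continuous score only. The planned sample size is unaffected.

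**What to change.** Before unblinding, state that the main IBS-SSS score analysis is an ANCOVA: week-8 score on arm and continuous baseline IBS-SSS, reported with its 95% confidence interval. Remove the condition of appropriateness for this model. The lifestyle covariates can stay as a further sensitivity analysis.

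Do the same for each secondary continuous outcome whose own baseline is collected, using that outcome's baseline and not a shared list.

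If an adjusted logistic model for response is kept, include baseline severity band as well as baseline score. Label it supporting, and make no claim that it narrows the odds-ratio interval.

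For IBS-SSS the cost is a few sentences and one degree of freedom, with no new data, visits or patients. If the change is made in the protocol and not only in the analysis plan, it follows the amendment route in the Ethics section: ethics committee approval and an update to the registry.

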#### Concomitant treatment

If the participant is unable to tolerate the IBS-D symptoms or is dissatisfied with the therapeutic effects of TXYF during the treatment, pinaverium bromide (the first-line recommended drug in American Gastroenterological Association Institute Guidelines on the Pharmacological Management of Irritable Bowel Syndrome [27]) or other medications recommended by guidelines will be allowed to be taken by the patient. No matter what medications the patient uses, the medication’s name, dosage and duration of administration will be recorded in detail in CRF.

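### The second adjusted analysis treats on-study concomitant treatment as unaffected by allocation, although the protocol makes its use a reaction to how well the allocated granules work

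*Protocol article*

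**What the plan says.** Under Statistical description and statistical analysis methods, the protocol article compares groups by simple or multiple linear regression for continuous outcomes, and by chi-squared tests with logistic regression where needed for categorical ones. It then adds: "Two preadjusted analyses will be conducted, if appropriate". Of these, "The first preadjusted regression analysis included only baseline variables", with age, gender, smoking and drinking as examples. The other goes further: "The second preadjusted analysis will also adjust for concomitant treatment, a variable thought to be associated with outcome but not affected by treatment allocation". For categorical outcomes, the adjusted analyses will "adjust for the same covariates as those described for the continuous outcomes".

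Both forms of the primary outcome are therefore covered, since under Primary outcomes "we will not only compare the scores after treatment between groups, but also compare the response rate".

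The Concomitant treatment section allows pinaverium bromide or another guideline-recommended drug when a participant cannot tolerate the IBS-D symptoms or "is dissatisfied with the therapeutic effects of TXYF during the treatment". For whatever is taken, the drug name is noted and its "dosage and duration of administration will be recorded in detail in CRF".

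**The concern.** A covariate measured after randomisation is safe to adjust for only if allocation does not influence it. The protocol asserts this for concomitant treatment, but its own description makes the treatment a reaction to poor symptom control. If TXYF relieves symptoms, fewer TXYF than placebo participants will reach for rescue. Rescue then marks poor response and lies downstream of allocation, and conditioning on it compares groups that randomisation no longer balances.

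At stake is the reading of one conditional model for the primary score and response. Someone told that the covariate is unaffected by allocation has no reason to distrust that model. If it gave a smaller effect than the main comparison, part of a real benefit could be put down to rescue use.

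**Working it through.** **Step 1: the sections side by side.**

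- Timing. The inclusion criteria admit only "patients who have not taken any medications related to the treatment of IBS-D at least 1 week before enrolling the trial". The Concomitant treatment section places rescue within the treatment period. The analysis section sets this model apart from one restricted to baseline variables. On-study IBS medication is therefore a post-randomisation variable.
- Trigger. It is intolerable symptoms or dissatisfaction with the effect. Both depend on how well the granules work. Blinding does not remove this, because the trigger is symptoms and perceived effect, not knowledge of the arm.
- Planned effect. The Sample size section assumes response of 73% v 43%, so non-response is 27% v 57%. Under that assumption, the pool from which rescue users mainly come is 57/27 = 2.1 times as large on placebo.

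The stated reason can hold only if TXYF does not change the symptoms that trigger rescue.

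**Step 2: inputs for an illustration.** From the document: 73%, 43% and 48 per arm. Assumed, because the document gives none of them: normal scores with SD 1; a share u = 10%, 30% or 40% of placebo non-responders taking rescue; and a rescue benefit r of 0, 1 or 1.5 SD.

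- Score difference implied by the response rates: d = z(0.73) − z(0.43) = 0.613 + 0.176 = 0.789 SD.
- Unadjusted odds ratio: (0.73/0.27)/(0.43/0.57) = 3.58.
- Rule A: a random share u of non-responders in each arm takes rescue.
- Rule B: anyone whose score is above z(1 − 0.57u) takes rescue, so the worst patients are rescued.

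**Step 3: inert rescue (r = 0).** The as-randomised and no-rescue effects are then both 0.79 SD and OR 3.58, so any departure comes from the adjustment alone. With arm and rescue in a linear model, the arm coefficient averages the within-stratum differences with weights proportional to n1·n0/(n1+n0).

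Example, rule B with u = 30%:

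- The threshold is z(0.829) = 0.950. Rescue use is 0.171 on placebo and 1 − Φ(0.950 + 0.789) = 0.041 on TXYF.
- Among rescue users, the difference in means is 0.130 with weight 0.171 × 0.041/0.212 = 0.033. Among the rest it is 0.574 with weight 0.829 × 0.959/1.788 = 0.445.
- Adjusted difference: (0.033 × 0.130 + 0.445 × 0.574)/0.478 = 0.54 SD.
- With inert rescue every user is a non-responder, so the adjusted OR comes from the no-rescue stratum: [0.73/(0.959 − 0.73)]/[0.43/(0.829 − 0.43)] = 2.96. Under rule A the factor (1 − u) cancels and the OR stays 3.58.

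| Rule | u | Users per 48, TXYF v placebo | Adjusted difference (SD) | Adjusted OR |
|---|---|---|---|---|
| A | 10% | 1.3 v 2.7 | 0.76 | 3.58 |
| A | 30% | 3.9 v 8.2 | 0.70 | 3.58 |
| A | 40% | 5.2 v 10.9 | 0.66 | 3.58 |
| B | 10% | 0.4 v 2.7 | 0.68 | 3.34 |
| B | 30% | 2.0 v 8.2 | 0.54 | 2.96 |
| B | 40% | 3.0 v 10.9 | 0.49 | 2.80 |

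**Step 4: effective rescue.** The adjusted score difference does not depend on r, but the as-randomised one does.

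- Rule A, r = 1 SD: as-randomised 0.76, 0.70, 0.67; adjusted 0.76, 0.70, 0.66. They practically match.
- Rule B, r = 1 SD: as-randomised 0.74, 0.66, 0.62; adjusted 0.68, 0.54, 0.49. Adjusted is lower.
- Rule A, u = 40%, r = 1.5 SD: as-randomised 0.61; adjusted 0.66. Adjusted is higher.

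The adjusted OR does change with r. At u = 40% and r = 1 SD it is about 3.4 under rule A, against about 3.3 as-randomised, and 2.69 under rule B.

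**Step 5: a second model.** Suppose rescue starts when mid-treatment symptoms are high, with a true effect of 0.3 to 0.8 SD (80% of it present by then), a placebo rescue rate of 16% or 31%, and a rescue benefit of 0 or 0.3 SD. Adjustment then shrinks the estimate by about 9% to 22%, for example from 0.60 to 0.48 SD. With no true effect, rescue is equal in both arms and the adjustment causes no bias.

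**The case against.** The strongest case on the other side concerns weight and certainty.

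- **Reach.** Only the second of two conditional analyses uses the covariate. The chi-squared test, the simple regression and the baseline-adjusted model do not. This stands. A reader might infer that the trial's main comparison is compromised; nothing in the protocol supports that. Nor does it say that the second model would override or refine the main result.
- **No estimand at all.** A reader might infer that the adjusted model can never recover a meaningful effect. That is too strong: under rule A with inert rescue, the adjusted OR is 3.58, equal to both targets. The supportable statement is that it need not equal either.
- **Always diluted.** A reader might also infer that adjustment must understate the benefit. Step 4 shows that it can match or slightly exceed the as-randomised value, so direction depends on inputs that the document does not give.
- **Size.** The largest fall, 0.79 to 0.49 SD, needs 40% rescue among placebo non-responders, strict selection of the worst patients and a guideline drug that does nothing. At a 1 SD benefit, the shortfall from the as-randomised value is at most about 0.13 SD, less than the standard error of the comparison (√(2/48) = 0.20 SD). This stands: the figures show what is possible, not what to expect.
- **Benign reading.** Entry bars only IBS-D drugs, so background medication for other conditions could fall under the label and be a baseline feature. This is weak: the section that describes concomitant treatment gives IBS symptoms and dissatisfaction as the triggers.
- **Left to the analysis plan.** The unseen plan may settle how rescue is handled. But the article does not defer this point. It names the covariate and gives a reason that its own text contradicts.

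**Conclusion.** The concern holds in this limited form. The reason given for adjusting for concomitant treatment contradicts the protocol's description of that treatment, and nothing else in the article corrects it. Whenever TXYF works, the second adjusted estimate, for score and for response, need not equal the as-randomised effect or the effect without rescue.

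That conclusion rests on the text. The size rests on assumed rescue rates, rescue benefit and normal scores. With inert rescue, 0.79 SD becomes 0.49 to 0.76 SD and the OR lies between 2.80 and 3.58. With effective rescue, either direction is possible. No bias is expected if TXYF has no effect, so the documents give no ground for alleging a false-positive risk. The correction should be made, but it does not threaten the main comparison.

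**What to change.** Delete the clause saying that allocation does not influence concomitant treatment. Remove on-study concomitant treatment from the covariates for continuous and categorical outcomes, and adjust only for baseline variables, as the first adjusted analysis does. Keep the ITT comparison, regardless of rescue, as the main result for score and response. Tabulate rescue use by arm from the drug details already recorded in the CRF.

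A supplementary response analysis that scores rescue users as non-responders is optional, and the error does not require it. It can itself be diluted: the planned 30.0-point difference stays at 30.0 if only non-responders take rescue, but becomes 30.0 × 0.9 = 27.0 points if 10% of would-be responders in each arm also do.

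The cost is one corrected sentence and the loss of one optional model. No new data are needed.
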